### Sample size

In qualitative research, the sample size cannot be conclusively estimated since it is determined by the saturation of the data acquired during the analysis of the qualitative data (e.g., semi-structured interviews). However, the sample size in SS1 has been estimated as n = 10, based on similar studies assessing the acceptance of a mobile solution, wherein the sample size for interviews and feasibility pilots was between 10–20 participants [36, 37]. Data saturation in the qualitative thematic analysis is expected to be achieved in less than ten subjects due to the focused nature of the study. In the case that this saturation is not achieved, the sample will be extended to include ten more participants.

In SS2, a sample size of n = 55, has been estimated by the GPower v.3.1.9.2 software. Specifically, a study design with 55 participants is appropriate to detect a low-to-medium effect size (Cohen’s *d* = 0.40) with a probability of α = 0.05 associated with a power of 1—ß = 0.08. The estimation is based on mean group differences between the baseline assessment and 3-months of follow-up (i.e., two-sided one-sample t-test).

Participants will be followed after Informed Consent Form (ICF) signature at the hospital to the end of the data collection period. It should be noted that in SS1, participants would engage with the solution for 1 month after recruitment. Since SS1 mainly focuses on usability, we estimated a period of one month, so that participants have a reasonable time to test the DH solution and subsequently rise concerns, barriers or facilitators when using the app. During this one-month observation time, participants will be supported if any doubt or concern arises.

In SS2 participants will be able to engage with the solution, for 3 months. The timing has been established on the standard mindfulness-based training programs that last a minimum of eight weeks [38]. Since the DH solution is self-administered, we added one extra month so that participants have more time to engage with the proposed activities. Major protocol amendments, if any, will be rigorously handled and updated at the ClinicalTrials.gov registry. The present study protocol has been elaborated following the recommendations for study protocols [39] based on the CONSORT extension statement for feasibility trials and the Standard Protocol Items: Recommendation for Interventional Trials (SPIRIT; see Additional file 1).

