### Data analysis plan

Qualitative data in SS1 will be gathered by means of video/audio interview recordings, which need to be transcribed and coded, first, to be able to manage a more standard dataset. Subsequently, all recordings will be deleted to preserve participants’ anonymity. At least two different reviewers conduct data analyses, independently. Through the iterative process, themes and subthemes will be identified and coded as barriers or facilitators associated with the use of the eHealth solution (Deductive part). Thematic content analysis will be performed afterwards (Inductive part) (37, 54). Descriptions of demographic, clinical, and usability data will be reported in a specific section.

Quantitative data in SS2 will be gathered in a different dataset. Descriptions of demographic and the study outcomes (frequencies, mean, standard deviation, median, maximum-minimum values data, skewness, and kurtosis) will be reported in a specific section. To analyze intervention effects on the primary outcome (i.e., Positive Affect), one sample t-test between baseline and 3-month follow-up scores will be performed. Similarly, pre-post data regarding the secondary outcomes (I.e., psychological distress, self-efficacy, mental wellbeing, and children’s quality of life) will also be examined by t-tests. Bonferroni correction will be used to account for multiple comparison testing. A non-parametric approach (I.e. Mann- Whitney *U* test) will be used in the case that the data shows departures from normality distributions.

In addition, exploratory analyses will also include correlations to identify relevant associations between demographic, primary, secondary outcomes, as well as, childrens’ QoL, treatment adherence, and usability.

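### The switch to a Mann-Whitney U test when data look non-normal is unnecessary at n = 55, abandons the mean change on which SS2 was sized, and names a test that ignores pairing

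*Protocol article*

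**What the plan says.** All references are to the Methods of the protocol article.

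- **Data analysis plan, primary outcome (positive affect).** A "one sample t-test between baseline and 3-month follow-up scores will be performed".
- **Data analysis plan, secondary outcomes.** The domains "psychological distress, self-efficacy, mental wellbeing, and children’s quality of life) will also be examined by t-tests", and "Bonferroni correction will be used to account for multiple comparison testing".
- **Data analysis plan, fallback.** A rank test, named as the Mann-Whitney U test, "will be used in the case that the data shows departures from normality distributions". The sentence follows both the primary and the secondary analyses and exempts neither.
- **Sample size.** "The estimation is based on mean group differences between the baseline assessment and 3-months of follow-up", by a two-sided one-sample t-test with d = 0.40 and n = 55. No rank test enters the calculation.
- **Design and setting.** SS2 is a single group assessed before and after use of the app, so each caregiver supplies a pair of scores.

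**The concern.** The rule lets the outcome data decide, outcome by outcome, which quantity is tested. The t-test addresses the mean change. The Mann-Whitney U test addresses whether a follow-up score tends to exceed a baseline score, as if the two came from different people. A signed-rank test, the natural paired substitute, addresses the centre of symmetry of the changes, which equals the mean only if the changes are symmetric.

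Three things are at stake. The primary outcome may lose the analysis on which SS2 was sized. Different outcomes may be reported on different quantities. And the Discussion places this study on the path to a randomised trial, whose planning needs mean changes and their standard deviations.

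**Working it through.** **Inputs from the protocol:** n = 55 pairs, d = 0.40 (mean change divided by the SD of the change), two-sided alpha 0.05, one-sample t-test. The power is printed as 0.08. It is read here as 0.80, a separate slip on which nothing below depends.

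**Assumed, because the protocol gives no figure:** pre-post correlation ρ of 0.3 to 0.7; skewness of the change from 0 to 2 (gamma shapes); Shapiro-Wilk at 5% wherever a normality check is simulated.

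**1. The plan's own figure.** The noncentrality is 0.40 × √55 = 2.966 on 54 degrees of freedom, which gives power 0.830. Power 0.80 needs 52 (0.808; 51 gives 0.7999). So 55 is slightly more than the stated test requires, and is adequate.

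**2. Is the switch needed?** The t-test requires only that the mean of the 55 differences be roughly normal. The table shows rejection under a zero mean change at nominal 5%, simulated with 20,000 trials per case. The signed-rank column has no pretest.

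| Change distribution | t-test always | Signed-rank always | Shapiro-Wilk, then t or signed-rank |
|---|---|---|---|
| Normal | 5.1% | 5.0% | 5.2% |
| Symmetric, heavy tails (t, 5 df) | 4.8% | 5.1% | 5.0% |
| Skewness 0.5 | 5.2% | 6.3% | 6.1% |
| Skewness 1.0 | 5.5% | 9.8% | 9.7% |
| Skewness 1.4 | 5.6% | 14.5% | 14.5% |
| Skewness 2.0 | 6.4% | 24.5% | 24.5% |

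Separate runs at skewness 1.5 gave 15% to 17% for the two-stage rule. At alpha 0.01 (Bonferroni with five outcomes, an illustration, since the number of comparisons is not stated) the t-test gives 1.3% at skewness 1.0, 1.6% at 1.4 and 2.2% at 2.0. It is less exact there, which is a reason for a bootstrap check. The signed-rank test gives 2.5%, 4.8% and 9.6%.

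The last two columns of the table agree. The excess comes from the quantity the signed-rank test addresses, not from looking at the data first.

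**3. The test actually named.** Let the score SD be 1. The SD of the change is then √(2(1−ρ)), so d = 0.40 is a shift of 0.40 × √(2(1−ρ)). A test for independent groups sets this against √(2/55). Its expected z is 2.966 × √(1−ρ), while the true SD of the statistic is only √(1−ρ). For a mean-based test this gives power ≈ Φ((2.966√(1−ρ) − 1.96)/√(1−ρ)) and a false-positive rate ≈ 2Φ(−1.96/√(1−ρ)).

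| ρ | Expected z | Approximate power | Simulated Mann-Whitney power | Approximate false-positive rate |
|---|---|---|---|---|
| 0.3 | 2.48 | 0.73 | 0.70 | 1.9% |
| 0.5 | 2.10 | 0.58 | 0.55 | 0.6% |
| 0.7 | 1.62 | 0.27 | 0.26 | below 0.1% |

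The planned t-test has 0.83 at every ρ. These are properties of the Mann-Whitney test itself; with exactly normal scores the switch would seldom fire.

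**4. A case where the switch does fire.** Raw scores have skewness 1.5 and are exchangeable before and after. Shapiro-Wilk on the baseline scores fires in 98% of trials. The t-test is still sound: 4.8% to 5.0% false positives, power 0.82 to 0.83. Under the switch the rule gives 0.2% to 2.3% false positives and power 0.89, 0.80 and 0.56 at ρ = 0.3, 0.5 and 0.7. At low correlation the rank test gains power; at high correlation it loses much.

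**5. Other shapes, two-stage rule with Mann-Whitney, ρ 0.3 to 0.7.** With skewed mean-zero changes and normality checked on the changes: 1.8% to 2.6% at skewness 1.0, and 0.0% to 1.1% at 2.0. With normality checked on the scores: 4.5% to 5.5%. If the score shape moves from normal to exponential at equal mean: at most 7.4%, reaching 10.8% only at ρ = 0.

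**The case against.** The fallback is stated in advance, in a single-group exploratory study. The diagnostic, its threshold, and whether scores or changes are checked are details that an article may leave to the analysis plan. That stands, and no fault is found with those omissions. What the article does fix is that the test changes with the data, and that the replacement is the Mann-Whitney U test.

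A reader might infer that the rule doubles or triples the false-positive rate. The protocol does not support that reading, for three reasons.

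- Rates of that size belong to a signed-rank test, which the protocol does not name. The test it names is mostly conservative on positively correlated pairs.
- They need marked skewness of the changes, about 1.0 for doubling and 1.4 for tripling. The protocol gives no figure for this. There is no excess for symmetric changes, and about one percentage point at skewness 0.5.
- They are not caused by the normality check, since the signed-rank test alone gives the same rates.

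It can also be said that a skewed change with mean zero is still a change, so that rejecting is not plainly an error. That is fair as a statement about rank tests. It does not help here, because the sample size section defines the effect as a mean difference.

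**Conclusion.** The point holds in this form. The switch covers the primary outcome, is unnecessary at n = 55, and replaces the quantity on which SS2 was sized. With the test as printed, the main harm is lost power: 0.70, 0.55 and 0.26 against 0.83 at d = 0.40, for normal scores and ρ = 0.3, 0.5 and 0.7. The loss is not universal, since with strongly skewed scores and ρ = 0.3 the rank test does better.

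Renaming the fallback as a signed-rank test would cure the pairing but not the change of quantity: rejection under a zero mean change would be about 10% to 17% at change skewness 1.0 to 1.5.

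Every rate here rests on assumed shapes and correlations. The conclusion that the t-test needs no replacement depends least on them, as its rate stays between about 5% and 6.4% at nominal 5% across the shapes tabulated.

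**What to change.** In the data analysis plan:

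1. Delete the sentence that makes the test depend on normality.
2. State that, for every primary and secondary pre-post outcome, the mean paired change is analysed by the planned one-sample t-test with a 95% confidence interval, whatever the distribution.
3. Add a bootstrap interval for the mean change as a check.
4. If a rank-based result is wanted, name the Wilcoxon signed-rank test, not the Mann-Whitney U test, as a sensitivity analysis that does not replace the main one.

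The cost is wording only; sample size, visits and data collection do not change. The downside is some loss of power relative to a paired rank test if the changes are symmetric with heavy tails. In the skewed-score case in step 4, the t-test still kept 0.82 to 0.83, the power it has at n = 55 under normality.

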## Results

The recruitment process for the SS1 is planned to start by June 2021 and the qualitative analysis is expected to be done by September 2021. Regarding SS2, the recruitment process is planned to start by January 2022 and the primary impact analysis is foreseen to be conducted by February 2023. This protocol describes a novel approach to the mental wellbeing of caregiver of children undergoing a stressful treatment such as the GHt. Furthermore, the protocol presents a scalable tool showing how a collaboration between companies and public health care system might promote such technology into the global health care market.

According to our research questions and hypothesis, we will expect that:In SS1, the usability of the designed DH solution will be acceptable. Furthermore, in SS2 we expect high scores in the SUS (Hypothesis 1).A decrease on the levels of psychological depression, anxiety, and measured by the DASS-21 (Hypothesis 2)An improvement of positive affect (by the PANAS), self-efficacy (by the GSE), and mental wellbeing (by the MHC-SF), and particularly, emotional and psychological wellbeing. (Hypothesis 2)Finally, those psychological variables are positively associated with the children’s quality of life and treatment adherence. (Hypothesis 3).

## Discussion

The study protocol aims to investigate the usability user experience and the intervention feasibility of Adhera Caring DH that has been developed upon principles of technology acceptance [25]. The results of this study will provide relevant information to support the mental well-being of caregivers, in this case of children undergoing GHt but with the long-term goal that the Adhera Precision Digital Companion Platform will be used and its effectiveness evaluated by caregivers of children with different clinical conditions, such as diabetes mellitus and chronic diseases with prolonged subcutaneous treatments (e.g., immunodeficiencies, rheumatological diseases). CBT and MBCT have been proposed as the main techniques to increase, on one hand, the caregivers’ awareness of their children’s medical condition, their own useless and negative thoughts and related-behaviours, reframing them with positive and useful thoughts and behaviours; and on the other, to provide activities to support patients to pay attention to their thoughts without judgment, accepting them and reducing the impact of negative and useless thoughts and behaviours, thus, providing tools to cope with the stressful situations. Changes of caregivers’ negative thoughts and affect states into positives could have relevant implications into the treatment adherence, quality of life and children development [6, 15]. Indeed, caregivers represent the first source for a healthy children mental wellbeing development and in the current healthcare system it is hard to provide caregivers’ support and DH interventions can provide it on a larger scale which would be reflected in the future quality of life in the long term. However, more research is needed on both the usability and the effectiveness of this type of intervention to achieve a randomized control trial and Adhera Caring fits into this research framework.

According to this, it is also relevant to present some limitations of the actual DH research and the future challenges. Among these limitations, the intervention does not investigate potential effects of each of the three modules (I.e., educational, behavioral change, and mental wellbeing) in isolation but as a whole. In this regard, own prior research demonstrates that motivational messages following a behavioral-change model can be effective in the context of smoking cessation [26]. Therefore, further research is needed to clarify the concrete impact of these components in the particular context of a DH solution targeting caregivers of children undergoing GHt. Another limitation is that children involved in the study can be at different GHt intervention stages. In this regard, it is reasonable that caregivers’ concerns and mental health (e.g., psychological distress) could also be heterogeneous. Future studies could investigate effects of the intervention in recently diagnosed children so that parent can get presumably more profit of the content delivered by the DH solution.

## Data Availability

Not applicable.

## Abbreviations

AI: Artificial intelligence
CEICA: Aragonese ethical committee for clinical research
CBT: Cognitive beahavioral therapy
CONSORT: Consolidated standards of reporting trials
DASS: Depression, anxiety, stress scale
eCRF: Electronic case report form
EHR: Electronic health record
GDPR: General data protection regulation
GHt: Growth hormone therapy
GSE: General self-efficacy
HCP: Healthcare professional
HrQoL: Health-related quality of life
ICF: Informed consent form
ICH GCP: International conference on harmonization and good clinical practice
IRB: Institutional review board
LMM: Linear mixed model
MANOVA: Multivariate analysis of variance
MBCT: Mindfulness-based cognitive therapy
MHC-SF: Mental health continuum-short form
PANAS: Positive and negative affect scale
QoLISSY: Quality of life in short-statured youth
SGA: Small for gestational age
SPIRIT: Standard protocol items: recommendation for interventional trials
SS1: Sub-study 1
SS2: Sub-study 2
